## Abstract

**Background:**

The prognostic benefits and safety of extended lymphadenectomy for hilar cholangiocarcinoma remain uncertain. The available evidence is still insufficient concerning its retrospective aspect. The aim of this study is to explore the clinical effect and safety of extended lymphadenectomy compared to regional lymphadenectomy in patients with hilar cholangiocarcinoma.

**Methods:**

The Relay-HC trial is a prospective, multicenter, and randomized controlled trial. Seven hundred and thirty-four eligible patients with resectable perihilar cholangiocarcinoma across 15 tertiary hospitals in China will be randomly assigned (1:1) to receive either regional lymphadenectomy or extended lymphadenectomy. The primary objective is to determine the overall survival after the two approaches. Secondary objectives of the study include the evaluation of perioperative mortality, postoperative complication, and disease-free survival. This study has been approved by the ethics committee of each participating hospital.

**Discussion:**

The Relay-HC trial is designed to investigate the prognostic benefits and safety of expanded lymphadenectomy for hilar cholangiocarcinoma. Currently, it has never been investigated in a prospective randomized controlled clinical trial.

**Trial registration:**

Chinese Clinical Trial Registry (ChiCTR), ChiCTR1800015688. Registered on 15 April 2018.

**Electronic supplementary material:**

The online version of this article (10.1186/s13063-019-3605-z) contains supplementary material, which is available to authorized users.

## Background

Hilar cholangiocarcinoma is one of the most common bile duct cancers, accounting for 60–70% of extrahepatic cholangiocarcinomas. Surgical resection remains the mainstay of potentially curative treatment for hilar cholangiocarcinoma. However, the probability of radical curative resection is low, and the prognosis is insufficient [1–3].

The incidence of lymph node metastases is high on the presentation or exploratory laparotomy. As the prognosis of patients with nodal metastases is significantly worse, the American Joint Committee on Cancer (AJCC) has modified the staging of lymph nodes invasion (N) several times during the last decade. However, concerning lymphatic dissection, there are still many disputes [1, 4, 5], and currently, no consensus has been reached on the preferred method of lymphadenectomy in patients with hilar cholangiocarcinoma. The incidence of complications after extended and regional lymphadenectomy has only been assessed in small retrospective series.

We hypothesize that extended lymph node dissection (8a/p, 9, 12a/b/c/h/p, 13a, 14, 16) might improve the prognosis of the patients without elevating the major complication rate. Therefore, the primary objective is to determine the overall survival (OS) rate for the two approaches with the secondary endpoint of perioperative mortality, postoperative complications, and disease-free survival (DFS). This study will explore the prognostic benefits and safety of extended lymphadenectomy for hilar cholangiocarcinoma.

## Methods

### Design

The Relay-HC trial is a prospective, multicenter, randomized controlled trial. Patients who will receive curative radical resection for hilar cholangiocarcinoma would be randomly assigned (1:1) to receive either regional lymphadenectomy or extended lymphadenectomy. The sample size calculation resulted in a requirement of 734 patients. On the basis of previous data, the median 5-year OS of patients with hilar cholangiocarcinoma who underwent regional lymphadenectomy (P1) was 0.17 (0.07–0.20) [6–9], and the 5-year OS for those with extended lymphadenectomy (P2) was 0.26 [3, 10, 11]. The α level (type I error) is set as 0.05 (one-sided), β is set as 0.2, and the power is set as 0.8. The formula to calculate the sample quantity for a high-quality clinical trial is [12]:
$$ {n}_1={n}_2=\frac{\Big[{u}_a\sqrt{2p\left(1-p\right)}+{u}_{\beta}\sqrt{p_1\left(1-{p}_1\right)+{p}_2\left(1-{p}_2\right)\Big]{}^2}}{{\left({p}_1-{p}_2\right)}^2} $$

The minimum sample size for each group is 330. As the actual sample size includes 10% shedding, the actual sample size of each group is thus 367 patients.

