The principal analysis consists of an intention-to-treat comparison of the major complications in both groups, using a Mann-Whitney *U* test for ordered categorical data with a two-sided 0.05 significance level. The proportion of patients with any severe operation-related complication will also be expressed in terms of relative risk (RR) and 95% confidence interval (CI). Categorical variables are evaluated using Pearson’s χ^2^ test or Fisher’s exact test.

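### The stated one-sided 0.05 level, 80% power and 330 patients per group cannot all be right: the printed formula gives 257, and the level of the primary survival test is left unclear

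*Protocol article*

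**What the plan says.** The sample size paragraph of the protocol article (Methods, Design) gives every input to the calculation. For regional lymphadenectomy the 5-year survival rate is 0.17, a literature median with a range of 0.07 to 0.20. For the other arm, "the 5-year OS for those with extended lymphadenectomy (P2) was 0.26". The error rates are given as "The α level (type I error) is set as 0.05 (one-sided), β is set as 0.2, and the power is set as 0.8". The formula for comparing two proportions in equal groups is printed, and the result is "The minimum sample size for each group is 330". A 10% loss allowance raises this to 367 per group, 734 in total.

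Observation indices names the 5-year overall survival rate as the primary endpoint. Statistical analysis compares overall survival by log-rank test and Cox regression, with no level or sidedness. The one level in that section belongs to the comparison of major complications, which uses a Mann-Whitney "test for ordered categorical data with a two-sided 0.05 significance level".

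**The concern.** The formula, its inputs and its result are all printed, so the result can be checked directly, and it does not follow from the inputs. The gap is 73 patients per group, too large for rounding. At least one of the level, the power, the rates or the size is misstated.

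This matters because the Design section is the only text from which a reader can take the significance level of the primary comparison. If the level is the wrong item, the article declares a primary test with twice the false-benefit risk that the size was built for. If the level is right, the stated power is wrong for 330 per group. While the question is open, a survival difference of moderate size could be called significant or not according to which reading is adopted, and that choice could be made after the data are seen.

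**Working it through.** **Inputs**, all from Design: p1 = 0.17, p2 = 0.26, difference 0.09, power 0.80 (u_β = 0.8416), allocation 1:1. The mean rate is p = (0.17 + 0.26)/2 = 0.215.

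**Formula as printed:** n per group = [u_α√(2p(1−p)) + u_β√(p1(1−p1) + p2(1−p2))]² / (p1−p2)².

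- √(2 × 0.215 × 0.785) = √0.33755 = 0.5810
- √(0.17 × 0.83 + 0.26 × 0.74) = √0.3335 = 0.5775
- (p1−p2)² = 0.0081

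**Step 1. The level as stated, one-sided 0.05 (u_α = 1.645).** n = (1.645 × 0.5810 + 0.8416 × 0.5775)² / 0.0081 = 256.6, so 257 per group. The stated 330 is not reproduced: 330 − 257 = 73, and 330/257 = 1.28.

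**Step 2. Two-sided 0.05 (u_α = 1.960), nothing else changed.** n = (1.960 × 0.5810 + 0.8416 × 0.5775)² / 0.0081 = 325.9, so 326 per group. This is 1.2% below 330.

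**Step 3. Other methods at the stated rates and power.**

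| Method | One-sided 0.05 | Two-sided 0.05 |
|---|---|---|
| Printed formula | 257 | 326 |
| Unpooled, pooled-only or arcsine forms | 255–258 | 323–327 |
| With continuity correction | 279 | 348 |
| Survival formulas (hazard ratio ln 0.26/ln 0.17 = 0.760) | 210–213 | 266–269 |

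No one-sided entry comes near 330.

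**Step 4. Power at 330 per group.** Solving the printed formula for u_β gives u_β = (0.09√330 − u_α × 0.5810)/0.5775, with 0.09√330 = 1.635.

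- One-sided 0.05: (1.635 − 0.956)/0.5775 = 1.176, power 88.0%.
- Two-sided 0.05: (1.635 − 1.139)/0.5775 = 0.859, power 80.5%.

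Only the second agrees with the stated 0.8.

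**Step 5. Loss allowance.** 330/0.9 = 366.7, so 367; 2 × 367 = 734. Both are correct, so the fault lies before this step.

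**Step 6. What the reading decides.** The standard error of the difference at 330 per group is about √(0.33755/330) = 0.0320. The smallest significant difference is about 1.645 × 0.0320 = 5.3 percentage points at one-sided 0.05, and 1.960 × 0.0320 = 6.3 points at two-sided 0.05. An observed benefit between these is positive under one reading and negative under the other. This is an approximation on the 5-year proportions, not on the log-rank statistic.

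**The case against.** A reader might infer that 330 can only have come from a two-sided 0.05 test and that the words on the level are therefore proven wrong. The document does not go that far. Two-sided 0.05 gives 326, not 330. One-sided 0.05 comes as close or closer if an input moves a little: p1 = 0.18 gives 330.5; rates of 0.175 and 0.255, at the edge of rounding to the printed values, give 325; power of 0.88 gives 330. The first and last of these contradict a printed figure, and the rounding case needs both rates to sit at their limits, so they are less simple than a change of sidedness. They still show that 330 does not by itself identify the level.

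A reader might also take the two-sided level in Statistical analysis as contradicting the one-sided level in Design. It does not: it is attached to the complications test. The survival hypothesis in Background is directional, so a one-sided survival test could be deliberate. In that case the type I error is exactly the stated 5%, nothing is inflated, and the trial is simply larger than its stated power requires.

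Nor should the survival figures in the Discussion be used to argue that a one-sided test is an error because it cannot show harm. The cited comparison has lower 5-year survival after extended than after regional dissection (12% against 31%), but it is reported as showing no significant difference in median survival. The limitation is common to all one-sided tests and is not a mistake in this document.

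Finally, 330 per group meets the stated 80% power on either reading, so the trial is not too small for its assumed rates. All of this stands. None of it reconciles the level, power, rates and size as printed.

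**Conclusion.** The point holds as an internal contradiction. With the printed formula and rates, one-sided 0.05 and 80% power require 257 per group, and the article states 330. A two-sided 0.05 calculation is the most plausible source, because it needs one change, lands within about 1% of 330 and restores the stated power. It remains an inference. A false-benefit risk of 5%, twice the 2.5% behind the size, follows only if the two-sided reading is the intended one.

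What is established is that the article leaves the error rate of its primary test open to two readings, 5% or 2.5% in the direction of benefit. That has to be settled before the survival data are analysed. The conclusion takes 0.17 and 0.26 at face value and p as their mean.

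**What to change.** State one significance level and its sidedness, and apply it by name to both the sample size and the primary overall survival test.

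- **Preferred:** two-sided 0.05 in both places, with 330 per group retained and the power given as 80.5%. The 367 per group and 734 in total then stand. Replacing the minimum by 326 would not fit those totals, since 326/0.9 = 362.2, or 363 per group.
- **If one-sided 0.05 is truly intended:** say so explicitly for the survival test and restate the power at 330 per group as 88.0%. Alternatively, give the formula minimum as 257, which becomes 286 per group and 572 in total after the 10% allowance.
- **If another input was used** (a different rate or power), print that input.

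The preferred change costs a sentence or two of text and no patients. Its only price is giving up the more lenient one-sided threshold. It should be dated before the survival analysis so that the choice cannot depend on the result.

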### Statistical analysis

Concerning the primary endpoint (overall survival), the log-rank test for univariable testing and Cox regression would be used to compare the long-term prognosis among patients in the extended lymphadenectomy group and the regional lymphadenectomy group in the intention-to-treat population. Secondary endpoints include DFS, survival without recurrence of regional nodal metastases, distant metastasis-free survival, the primary complication within 30 days after surgery (Clavien-Dindo grade > II), and perioperative mortality. Time zero is set as the time of randomization. After enrollment, all patients who have been randomized would be included in the full analysis set (FAS). On the basis of the FAS, patients who meet the inclusion and exclusion criteria (Table 1), are compliant, and do not violate the clinical trial protocol would form the per protocol set (PPS).

**Table 1 Tab1:** Eligibility criteria in Relay-HC trial

Inclusion criteria	
1. Age > 18 years old and ≤ 80 years old	
2. Diagnosis of hilar cholangiocarcinoma by preoperative imaging and laboratory examination; confirmed as biliary malignant tumor by intraoperative frozen and postoperative pathology; evaluated as resectable by preoperative imaging	
3. Preoperative CT/MRI shows no obvious lymph node metastasis of groups 9, 14 and 16	
4. Child-Turcotte-Pugh A–B grade of liver function	
5. Residual liver volume > 30% 6. ASA grade 1–3	
7. The patient has self-care ability, understands and voluntarily signs the written informed consent, and is able to complete the follow-up plan	
8. Female patients of gestational age must be excluded from pregnancy	
9. The patient has signed the written informed consent form before the screening test	
Exclusion criteria	
1. Tumor R1 resection	
2. The patient has obvious heart, lung, brain, or kidney dysfunction that affects the treatment of cholangiocarcinoma	
3. The patient has a history of other malignancies	
4. Child-Turcotte-Pugh C grade of liver function	
5. ASA grade 4–6	
6. Females who are pregnant or breastfeeding	
7. Patients who are not suitable for the study as determined by the researcher	

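### The stated 80% power comes from a two-proportion formula for 5-year survival and is not the power of the log-rank test planned for overall survival

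*Protocol article*

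**What the plan says.** All sizing statements are in the protocol article, Design. Allocation is 1:1. On survival at 5 years, "regional lymphadenectomy (P1) was 0.17" and "the 5-year OS for those with extended lymphadenectomy (P2) was 0.26". On error rates, "The α level (type I error) is set as 0.05 (one-sided") and "the power is set as 0.8". The section prints the pooled-variance formula for two independent proportions and concludes: "The minimum sample size for each group is 330". Dropout is then added: "As the actual sample size includes 10% shedding, the actual sample size of each group is thus 367 patients", which makes 734 in all.

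The Observation indices section names the 5-year overall survival rate as the primary endpoint. The Statistical analysis section calls the primary endpoint overall survival and says that "the log-rank test for univariable testing and Cox regression would be used to compare the long-term prognosis" in the intention-to-treat population. It gives no sidedness for that test. The article states no hazard ratio, number of deaths or log-rank power.

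**The concern.** The printed formula looks only at whether each patient is alive at 5 years. The log-rank test uses the order of all death times up to then. Its power depends on the number of deaths and on how the hazard ratio behaves over time, not on two survival proportions at one time point. The 80% was therefore worked out for one comparison and is attached to another.

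The power figure is what justifies the number of patients. If it does not belong to the test that will be run, a reader cannot tell how much margin the trial has. This matters more than usual here because the two operations differ in extent. The Discussion names added morbidity from extended dissection as a major worry for surgeons, so equal or worse early survival followed by later benefit cannot be dismissed.

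**Working it through.** **Inputs (Design section).** p1 = 0.17, p2 = 0.26, difference 0.09, mean p = 0.215, 1:1 allocation, power 0.80 (z = 0.8416), alpha 0.05 stated as one-sided (z = 1.6449). The two-sided value is z = 1.96.

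**Step 1. Reproduce the plan's 330.** The printed formula is n = [z_α √(2p(1−p)) + z_β √(p1(1−p1) + p2(1−p2))]² / (p1−p2)².

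- √(2 × 0.215 × 0.785) = 0.5810
- √(0.17 × 0.83 + 0.26 × 0.74) = √0.3335 = 0.5775
- One-sided 0.05: (1.6449 × 0.5810 + 0.8416 × 0.5775)² / 0.0081 = 256.6, so 257 per group
- Two-sided 0.05: (1.96 × 0.5810 + 0.8416 × 0.5775)² / 0.0081 = 325.9, so 326 per group

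The stated 330 is close to the two-sided result and far from the one-sided one. Continuity correction does not rescue the one-sided label (279 per group). The power of the two-proportion comparison at 330 per group is Φ[(√330 × 0.09 − z_α × 0.5810)/0.5775], which is 88.0% one-sided and 80.5% two-sided. The dropout step reproduces: 330/0.9 = 366.7, so 367.

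**Step 2. Power of the log-rank test at 330 per group.** Assumptions not stated in the article: proportional hazards, and every patient followed to death or 5 years.

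- HR = ln(0.26)/ln(0.17) = −1.3471/−1.7720 = 0.760; ln HR = −0.274
- Deaths by 5 years: 330 × (0.83 + 0.74) = 518
- Schoenfeld: power = Φ(½ √deaths × |ln HR| − z_α), and ½ × √518.1 × 0.2741 = 3.12

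| Alpha 0.05 | Two-proportion, n = 330 | Log-rank, Schoenfeld | Log-rank, Freedman | Log-rank, simulated |
|---|---|---|---|---|
| One-sided (as stated) | 88.0% | 93.0% | 92.7% | 92.8% |
| Two-sided | 80.5% | 87.7% | 87.3% | 87.7% |

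The simulation used 10,000 runs with exponential survival censored at 5 years. On neither reading of alpha is the log-rank power 80%.

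**Step 3. Sensitivity to hazard shape.** Keep 0.17 and 0.26 at 5 years, but assume that the curves coincide up to time t and separate only afterwards. The regional-arm hazard is 1.7720/5 = 0.3544 per year throughout. The extended-arm hazard after t is (1.3471 − 0.3544t)/(5 − t). Expected deaths remain 518.

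| Separation begins | Extended-arm hazard after t (per year) | HR after t | One-sided power | Two-sided power |
|---|---|---|---|---|
| At once | 0.269 | 0.76 | 93% | 88% |
| After 1 year | 0.248 | 0.70 | about 80% | about 70% |
| After 2 years | 0.213 | 0.60 | about 64% | about 53% |

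The delayed rows are simulated. The delay times are illustrative; the article gives no survival curves. The 5-year rates are the same in all three rows, so the two-proportion power stays at the values in Step 2 throughout. That is why the printed formula cannot stand in for the log-rank calculation.

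**The case against.** The best defence is that 0.8 is a design target, set beside β = 0.2, and not a claim about achieved log-rank power. The named primary endpoint is the 5-year survival rate, which is exactly what the formula compares, and 330 is called a minimum, so exceeding the target does no harm. This stands in part. Under proportional hazards the mismatch is conservative, and nothing here shows the trial to be too small. It does not remove the point, because the only test assigned to overall survival is the log-rank test with Cox regression. The chi-square and Fisher tests are mentioned for categorical variables in general, next to the complications analysis.

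A second objection is that a journal article may leave a target number of deaths to the full protocol or analysis plan. That is right, and the absence of an event target is not raised as a defect. The point is that a power figure that is printed belongs to a different test.

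Two stronger readings are tempting. A reader might infer that log-rank power is simply 88%. That is the two-sided value under proportional hazards; at the alpha that the article states it is 93%. A reader might also infer that 80% power is reached well before 5 years, or with fewer patients. The documents do not support this: it needs proportional hazards, which the article does not state, and moderate delay in separation takes two-sided power below 80% even with all 518 deaths.

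**Conclusion.** The point holds in this form: the stated 80% is not the power of the planned test of overall survival. At 330 per group the log-rank test has about 93% power at the stated one-sided 0.05 and about 88% at two-sided 0.05, given 5-year survival of 0.17 and 0.26, proportional hazards and complete 5-year follow-up. With the same 5-year rates and separation assumed to start after 1 or 2 years, two-sided power is about 70% or 53%, so the true figure may lie on either side of 80%.

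A separate discrepancy sits in the same paragraph: 330 and 80% agree for the printed formula only if alpha is two-sided (326 per group), not one-sided as written (257). Correcting the sidedness alone would restore about 80% for the proportion comparison but would still leave it unrelated to the log-rank test.

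This is a fault in the justification of the sample size. It is not evidence that 734 is the wrong number.

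**What to change.** Keep 734 patients and rewrite the sample-size paragraph in the Design section for the test named under Statistical analysis. It should:

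- state whether alpha is one-sided or two-sided, and use the same choice for the log-rank test;
- give the hazard ratio of 0.76 implied by 0.17 and 0.26;
- give about 518 expected deaths by 5 years at 330 evaluable patients per group;
- give about 88% power at two-sided 0.05 under proportional hazards and complete follow-up (about 93% if one-sided 0.05 is really meant);
- add the lower range under delayed separation, about 70% and 53% two-sided for delays of 1 and 2 years, labelled as assumed scenarios.

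It should not say that 80% power is reached early or with fewer patients. The cost is one paragraph; enrolment, follow-up and conduct do not change.

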### Case selection

All patients aged between 18 and 80 years old with hilar cholangiocarcinoma would be referred for a multidisciplinary team evaluation at each center. Hilar cholangiocarcinoma is defined as a cholangiocarcinoma that develops at the point where the left and right hepatic ducts join to form the common hepatic duct (as determined by computed tomography [CT] imaging or magnetic resonance cholangiopancreatography, or both). Criteria for resectable hilar cholangiocarcinoma include an anticipated complete (R0) resection with adequate future liver remnant (FLR > 30%) and Child-Turcotte-Pugh grade A–B, as well as American Society of Anesthesiologists (ASA) grades I–III. The residual liver volume will be assessed by three-dimensional reconstruction of CT images. These procedures will be accomplished by professional radiographers and the multidisciplinary teams from each center, who will be trained at the leading affiliation to ensure standardization. Patients who also have other malignancies would be excluded from the study.

### Setting

The study is performed at hepatobiliary surgery centers from 15 tertiary hospitals that receive the majority of patients with hilar cholangiocarcinoma from various parts of China. Each of the centers is qualified for standard radical resection of hilar cholangiocarcinoma and regional/extended lymph node dissection. The institutional review board at each hospital has approved the protocol. The number of cases for each center is allocated according to the number of annual cholangiocarcinoma surgeries. A flowchart of the study design was shown in Fig. 1.

